### Randomization and blinding

After signing the informed consent form, volunteers participating in the trial were randomly assigned to one of the two trial groups in a 1:1 ratio using stratified zone group randomization, and random numbers were generated using R software version 3.5.1. A strictly confidential list of randomization numbers will be maintained by the dosing center staff. Randomization will be stratified by trial center in different regions. The active drug (Guilu Xian) and placebo will be manufactured with similar appearance and smell. The clinicians and patients will be blinded to the drug allocation until the end of the study. If there are multiple adverse reactions in the trial, we will take emergency unblinding measures to find the cause of adverse events. To achieve high precision, the trial will follow the Consolidated Standards of Reporting Trials (CONSORT) 2010 statement [20] and the updated guidelines for reporting parallel-group randomized trials of the traditional Chinese medicine CONSORT [21].

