### Trial design

This is a prospective, randomized, placebo-controlled, double-blind, superiority trial assigned in a 1:1 ratio. The study institutions were the Genetic and Reproductive Center of Traditional Chinese and Western Medicine, Affiliated Hospital of Shandong University of Traditional Chinese Medicine, the Second Affiliated Hospital of Shandong University of Traditional Chinese Medicine, and Jinan Central Hospital. The project leader regularly coordinates and communicates with each unit to understand the progress of the project and ensure the smooth progress of the project and the guarantee of quality. In order to ensure that there are enough participants, we will take measures such as providing free basic examinations, free drugs, and car allowance to better attract participants to join.

The inclusion criteria for this study will be patients aged between 35 and 42 years old, with insufficient ovarian reserve parameters (The POSEIDON criteria AFC < 5, AMH < 1.1 ng/mL) [18], and poor ovarian response (that is, the number of oocytes obtained after standard ovarian stimulation is less than 3). Patients should meet the diagnostic criteria of western medicine infertility, that is, women living without contraception for at least 12 months who are not pregnant are infertile [19].

The exclusion criteria are women with BMI ≥ 25 kg/m^2^; women who suffer from genetic diseases that are not suitable for childbearing as stipulated in the Maternal and Child Health Care Law; women with severe endometriosis, adenomyosis, and immune infertility; with untreated hydrosalpinx; with congenital or acquired abnormal development of the uterus and severe deformities of other reproductive organs; women with a history of endocrine dysfunction such as reproductive system tumor, thyroid dysfunction, and hyperprolactinemia; women receiving ovarian stimulation therapy or OCP in recent 3 months; women with a previous history of gynecological surgery such as the ovary; and all other contraindications of assisted reproductive technology.

The discontinuation criteria will be women who have adverse reactions such as nausea and obesity occurring during medication, women with no dominant follicular growth, early follicular ovulation, and no egg acquisition during ovarian stimulation. Three days after egg harvesting, the embryo was not formed.

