### Estimation of the sample size

In a recent study in China, it was reported that in conventional IVF or ICSI, the total number of retrieved eggs in the treatment group (259.77±25.45) was significantly higher than that in the placebo group (235.59±26.44). In this study, the number of eggs obtained in the Guiluxian group was 11 under the original hypothesis and 9 under the alternative hypothesis (9 in the placebo group). The bilateral *Z* test of the combined variance will be used to estimate the sample size at 0.05 level of significance. The ratio between groups will be1:1. The minimum sample size found for each group is 49 people, hence a total of 98 people. Besides, 90% of the detection ability will be obtained, and the difference in ratio between groups is 0.15. Considering a dropout rate of 15%, we will be expected to enroll 120 participants, with 60 participants in each group (see supplementary files 1 and 2 for details).

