### Intervention

The Guilu Xian/placebo will be given to the patients at 5 g three times daily from the third day of their menstruation period before IVF for 40 days (provided by the preparation room of Affiliated Hospital of Shandong University of Traditional Chinese Medicine, and the extraction procedure will be based on the standard of preparation room SOP). Drug composition: tortoise glue, turtle glue, antler glue, Chinese wolfberry, American ginseng, Cornus officinalis, Hawthorn seed, jujube.

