### Supervision and management

We have also established a Data Monitoring Committee (DMC). The DMC is composed of the director of the Department of Reproductive Center of Shandong Provincial Hospital of Traditional Chinese Medicine as the chairman and the heads of the other two study sites as independent members. It is the responsibility of the DMC to monitor data, assess adverse events and cases of abnormal liver and kidney function results post-intervention on a regular monthly basis, review the core trial process, conduct interim analyses (the interim analysis includes the evaluation of the patient's follicular growth status, the number of retrieved oocytes and the incidence of adverse events. If the incidence of events of early follicular ovulation and absence of follicles after stimulation is as high as 30%, or the incidence of adverse events is as high as 10%, the trial will be terminated and the reasons for this will be analyzed.), and discuss relevant protocol amendments.

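### The unblinding trigger is trial-level and undefined; read literally it is likely to be met at reaction rates of about 3% or more, which puts the promised blind at risk

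*Protocol article*

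**What the plan says.** Under Randomization and blinding, the protocol article first makes the commitment: "The clinicians and patients will be blinded to the drug allocation until the end of the study". The next sentence is the unblinding rule: "If there are multiple adverse reactions in the trial, we will take emergency unblinding measures to find the cause of adverse events". The randomisation list is held in confidence by dosing-centre staff, and allocation is stratified by centre.

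Three other places bear on the rule:

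- Trial design lists among the discontinuation criteria "women who have adverse reactions such as nausea and obesity occurring during medication". Non-serious reactions are therefore foreseen, but no frequency is given.
- Intervention sets the exposure over which reactions can arise: "5 g three times daily from the third day of their menstruation period before IVF for 40 days".
- Supervision and management has a separate stopping rule: if "the incidence of adverse events is as high as 10%, the trial will be terminated". It does not mention unblinding.

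No section says how many reactions count as *multiple*, whether they must be serious or related to treatment, whether one woman, the affected women or the whole trial is unblinded, or who would learn the allocations.

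**The concern.** An emergency code-break normally concerns one participant whose care depends on knowing what she received. This rule is different in kind. It is triggered by events accumulating across the trial, it has no severity floor, and it serves to explain the events. Two mild reactions would satisfy the wording.

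If allocations became known to treating staff, several later steps could be affected. The choice of gonadotropin and hCG product and the choice between fresh and frozen transfer are left open under Ovarian stimulation and egg extraction and transplantation. Discontinuation for adverse reactions also involves judgement. These steps bear on the primary egg count and on secondary outcomes such as gonadotropin use and implantation. The randomisation also appears to be blocked within centre. If so, revealing some allocations would make others easier to guess, but the block size is not given and this point is secondary.

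The committee that assesses adverse events consists of the reproductive centre's director and the heads of the other two sites. The article names nobody outside the participating centres who would receive the codes.

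**Working it through.** The article attaches no figure to the unblinding rule, so there is nothing to reproduce. The check asks how often the trigger would be met, and how that compares with the 10% termination rule.

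**Inputs from the article.** n = 120 women, from Estimation of the sample size: "we will be expected to enroll 120 participants, with 60 participants in each group". The termination level is 10%, which is 0.10 × 120 = 12 women if counted once per woman over the full sample.

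**Assumed inputs.** The proportion p of women with a reaction is not stated, so 0.5% to 10% is shown. *Multiple* is taken at its literal minimum of 2, with 3 and 5 as alternatives. Women are treated as independent, and each is counted at most once.

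**Formula.** With X ~ Binomial(n, p),

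P(X ≥ 2) = 1 − (1 − p)^n − n p (1 − p)^(n − 1).

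For n = 120 and p = 0.03: 0.97^120 = 0.0259 and 120 × 0.03 × 0.97^119 = 0.0960, so P = 1 − 0.0259 − 0.0960 = 0.878.

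**Results, n = 120.**

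| Assumed rate p | P(X ≥ 2) | P(X ≥ 3) | P(X ≥ 5) | P(X ≥ 12), termination level |
|---|---|---|---|---|
| 0.5% | 12% | 2% | <0.1% | <0.1% |
| 1% | 34% | 12% | 0.7% | <0.1% |
| 2% | 69% | 43% | 9% | <0.1% |
| 3% | 88% | 70% | 29% | <0.1% |
| 5% | 98% | 94% | 72% | 1.7% |
| 10% | >99.9% | >99.9% | 99% | 54% |

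For at least 2 of 120, a 50% chance needs a rate of about 1.4%, a 95% chance about 3.9% and a 99% chance about 5.4%.

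**Sensitivity to n.** If only the 60 women on the active product were at risk, P(X ≥ 2) would be 34% at 2%, 54% at 3%, 81% at 5% and 99% at 10%. With 98 women, the article's minimum total before allowance for dropout, it would be 59%, 80%, 96% and >99.9%.

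**Direction of error.** The table counts women. One woman with two reactions also fits the wording, so for the at-least-2 reading the figures are a lower bound at a given p.

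**Comparison of the two rules.** Over the full 120, any reading of *multiple* from 2 to 11 is met before the termination level of 12. At p = 5% the unblinding trigger (at least 2) has a 98% chance of being met and the termination level a 1.7% chance. This assumes that the 10% is taken over all 120. If it is applied to the women treated so far, the two rules can coincide early on: 2 of the first 20 is already 10%.

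**The case against.** The strongest reply is that this is one loosely worded sentence in a condensed article, and that code-break procedure belongs in the full protocol. A general promise of blinding followed by an exception is not a contradiction. Nor is it inconsistent to look into causes at a lower threshold than the one for stopping the trial, particularly as one rule speaks of adverse reactions and the other of adverse events.

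The first part does not remove the point. The article does not leave the rule out; it states one, and nothing elsewhere narrows it. The exception reading is fair, but an exception this wide can take up most of the promise it qualifies. A lower threshold for investigation is reasonable in itself. The difficulty is that the stated means of investigation is unblinding.

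Two stronger readings are tempting, and the documents do not support them:

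- *The trigger is almost certain to be met.* This needs a reaction rate that the article does not give. At 1% the chance is 34%. If *multiple* means five or more, it is 9% at 2% and 72% at 5%. Naming nausea as an example of a reaction says nothing about its frequency.
- *Following the rule would break the double blind.* The text does not say whose codes are opened or who sees them. Code-breaks limited to affected women would harm the blind only in part, and some of those women would already meet a discontinuation criterion.

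The route to bias is also narrower than it may look. Gonadotropin is set at 300 IU, the antagonist and trigger criteria rest on follicle size or LH, and retrieval is timed at 36 hours. This limits the discretion through which knowledge of allocation could move the primary egg count. All of these qualifications stand.

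**Conclusion.** The point holds as a risk to the blind. The rule as published is trial-level, undefined in count, seriousness and scope, and aimed at finding a cause. With *multiple* read as at least 2 of 120 women, it is likely to be met at reaction rates of about 3% or more (88% at 3%, 98% at 5%), and at those rates it would usually be met in a trial that the termination rule lets continue. This rests on assumed rates, on the lowest reading of *multiple*, and on the 10% being counted over all 120 women. The extent of any damage depends on whose allocations are revealed and to whom, which the article leaves open. The sentence should be changed because the risk is avoidable at little cost.

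**What to change.** Reconcile the sentence with the blinding commitment before it and with the termination rule under Supervision and management, then replace the trial-level trigger with two provisions:

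1. Code-breaks are individual and are made only when knowing that woman's allocation is needed for her care. Each is logged, and the woman stays in the full analysis set, which already includes everyone randomised. The clinical criteria for a code-break are for the sponsor to set.
2. Clusters of adverse events are tabulated by arm from the list that dosing-centre staff already hold, without releasing allocations to treating clinicians, patients or embryologists.

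The cost is a short change to the protocol text. The one practical burden is that staff outside the treating teams must prepare the by-arm safety table. Neither the sample size nor any treatment rule changes.

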### Intervention

The Guilu Xian/placebo will be given to the patients at 5 g three times daily from the third day of their menstruation period before IVF for 40 days (provided by the preparation room of Affiliated Hospital of Shandong University of Traditional Chinese Medicine, and the extraction procedure will be based on the standard of preparation room SOP). Drug composition: tortoise glue, turtle glue, antler glue, Chinese wolfberry, American ginseng, Cornus officinalis, Hawthorn seed, jujube.

### Concomitant care

All subjects will not be allowed to take any other Chinese herbal supplements or nutritional supplements that may increase ovarian response for 3 months prior to the start of the study. Such drugs or nutritional supplements may affect the therapeutic effect of modified Guilu Erxian ointment.

### Placebo

The placebo was produced by the Affiliated Hospital of Shandong University of Traditional Chinese Medicine. The placebo was not different from Guilu Xian in appearance, color, and odor and had no active ingredients. On the one hand, can prevent participants from recognizing being assigned to a placebo group, and this may reduce participants’ compliance and on the other hand, it can prevent the potential beneficial effects of using vitamins as a placebo.

### Patient compliance

Assessment of patient’s compliance, including the bottle count of the drugs and weekly telephone follow-up, will be performed to find out if the participants are taking the medicine as agreed and any reasons for non-compliance. All unused drugs will be counted and registered. We will exclude patients with less than 70% compliance (i.e., in 40 days of treatment with Guilu fairy, while actually taking it for less than 28 days). They will not be included in the final analysis, but will be included in the intention-to-treat analysis.

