### Data analysis

All data are reported as mean ± standard deviation (SD). Patients with low adherence will not be included in the final analysis, but will be included in the intention-to-treat analysis. Two sets of analyses will also be performed for non-adherence and missing outcomes. The full analysis set (FAS) will include all patients who are randomized and will proceed according to the intention-to-treat principle. The protocol-compliant set will include all patients in the FAS who completed follow-up and did not experience a serious protocol violation.

For baseline comparisons, differences in means of continuous data between the placebo and intervention groups will be evaluated using independent Student’s *t* tests or Mann-Whitney *U* tests, depending on whether the data are normally distributed, and frequencies will be compared using chi-square tests. For longitudinal data with baseline, we will evaluate mean differences between and within groups using repeated measures analysis of covariance (ANCOVA). All tests will be two-tailed and ratios between the two groups will be compared using Fisher’s exact rate method with a significance level defined as a value < 0.05.

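### The label 'final analysis' goes to a set that drops women below 70% compliance, and the protocol never says that the intention-to-treat analysis carries the primary conclusion

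*Protocol article*

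**What the plan says.** The Patient compliance section states: "We will exclude patients with less than 70% compliance". It gives the threshold in days as "in 40 days of treatment with Guilu fairy, while actually taking it for less than 28 days", and then says of these women: "They will not be included in the final analysis, but will be included in the intention-to-treat analysis". The Data analysis section repeats it: "Patients with low adherence will not be included in the final analysis, but will be included in the intention-to-treat analysis". The rule is therefore stated twice and is not a slip in one place.

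The Data analysis section then announces two analyses, "Two sets of analyses will also be performed for non-adherence and missing outcomes", and defines two populations:

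- The first takes in everyone allocated to an arm: "The full analysis set (FAS) will include all patients who are randomized and will proceed according to the intention-to-treat principle".
- The second is a narrower subset of the first: "The protocol-compliant set will include all patients in the FAS who completed follow-up and did not experience a serious protocol violation".

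Neither population is called primary or final. The Trial design section describes a "double-blind, superiority trial assigned in a 1:1 ratio".

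**The concern.** In both places the final analysis is set against the intention-to-treat analysis as a different thing. The only word of priority in the text thus goes to a population selected on what happened after randomisation. In a superiority trial the main conclusion should rest on the women as randomised, because only that comparison is protected from selection.

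Compliance here may not be neutral with respect to the primary outcome, the number of eggs obtained. The discontinuation criteria under Trial design include adverse reactions, absent follicular growth, premature ovulation and failure to obtain eggs. A woman who stops early for one of these reasons could fall below 28 days and leave the final analysis. Selection would then act through tolerability or through the outcome itself.

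The number of days taken may also depend on how the cycle runs. The Abstract has dosing continue until egg retrieval, whereas the Intervention section gives 40 days. These statements need to be reconciled, because the 28-day cut-off is counted against the 40.

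If the two analyses disagree, the protocol gives no rule for which one answers the trial's question.

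**Working it through.** **The protocol's own figure.** 0.70 × 40 days = 28 days. The cut-off reproduces.

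**The populations side by side.**

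| Population | Who is in it | Role stated |
|---|---|---|
| Final analysis | Women with at least 70% compliance | Called final |
| FAS | All randomised, intention-to-treat | None stated |
| Protocol-compliant set | FAS members with completed follow-up and no serious violation | None stated |

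The first and third rows are not the same set unless compliance under 70% counts as a serious violation, and the protocol does not say so.

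**Inputs for an illustration.**

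- From the sample size section: 60 women per arm, two-sided alpha 0.05, 90% power, a difference of 11 − 9 = 2 eggs, and a minimum of 49 per arm.
- The SDs printed there belong to totals of 259.77 and 235.59, and none is given on the 11-versus-9 scale. I therefore assume the SD that makes 49 per arm give 90% power: SD = 2 × √(49/2) / (1.960 + 1.282) = 3.05 eggs.
- Assumed, because the protocol gives no such figures: the fraction excluded in each arm (f₁, f₂), and a deficit of k = 1 to 3 eggs in low compliers compared with compliers.

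**Bias when the true effect is zero.** Within an arm, the mean of the compliers exceeds the mean of all randomised women by f × k. Restricting to compliers therefore shifts the difference by (f₁ − f₂) × k.

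For 15% versus 5%:

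- Shift: 0.10 × 1 = 0.1 to 0.10 × 3 = 0.3 eggs. Against the protocol's 2-egg difference this is 0.1/2 = 5% to 0.3/2 = 15%.
- Women left: 60 × 0.85 = 51 and 60 × 0.95 = 57.
- Standard error: 3.05 × √(1/51 + 1/57) = 0.59.
- Type I error: 1 − Φ(1.96 − shift/SE) + Φ(−1.96 − shift/SE) = 5.3% at 0.1 eggs and 8.0% at 0.3 eggs.

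| Excluded, arm 1 vs arm 2 | Shift for k = 1 to 3 (eggs) | Type I error |
|---|---|---|
| 15% vs 15% | 0 | 5.0% |
| 15% vs 5% | 0.1 to 0.3 | 5.3% to 8.0% |
| 20% vs 5% | 0.15 to 0.45 | 5.7% to 11.7% |
| 30% vs 10% | 0.2 to 0.6 | 6.2% to 15.9% |

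The shift favours whichever arm loses more low-yield women.

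**Cost of using all randomised women.** Assume the same SD, outcomes for all 60 per arm, and no effect in non-compliers. If a fraction f in each arm is non-compliant, the difference falls to 2 × (1 − f), with standard error 3.05 × √(2/60) = 0.56. At f = 15% the difference is 1.7 eggs and power is 86.2%. At 0%, 10%, 20% and 30% power is 94.8%, 89.8%, 81.8% and 70.9%. The compliers-only analysis has a nominal power of 91.1% at 15%, but that figure ignores selection.

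**The case against.** The strongest reply is that the randomised comparison is not lost. Each of the two sentences keeps low compliers in the intention-to-treat analysis, and the FAS is defined as everyone randomised. Running an adherence-restricted analysis beside intention-to-treat is common and is no contradiction in itself. In a loosely worded article, 'final' may simply mean per-protocol. This stands, and it limits the point to the label and the missing hierarchy.

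It is also true that the protocol does not say that women discontinued under its criteria count as low compliers, or that compliance differs by arm. Matched placebo and blinding of patients and clinicians make a difference between arms less likely, though they cannot exclude one. The only 15% in the protocol is an overall dropout allowance, not split by arm. A one-sided loss on the active arm would be an assumption, as would any claim that the bias favours Guilu Xian.

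A reader might also note that eligibility requires fewer than 3 oocytes, scale the shift to an effect smaller than 2 eggs and obtain a larger percentage. That needs a mean egg count that the protocol does not give.

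The reply that an analysis plan may settle the hierarchy is weaker. The protocol does not leave the matter open: it assigns the final analysis explicitly, twice. A plan that made the FAS final would contradict this text.

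**Conclusion.** The point holds in a limited form. The protocol calls final an analysis restricted by a post-randomisation variable, and it never gives the planned intention-to-treat analysis the primary role. A superiority claim made as written could therefore rest on a non-randomised comparison.

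A reader might go further and infer that the headline result will be the compliers-only one, or that intention-to-treat has been abandoned. The text supports neither: no primary set is named, both analyses are planned, and nothing says which prevails if they differ.

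The harm is conditional. It is nil when exclusions and deficits match between arms. It is modest at 15% versus 5% exclusion and larger with greater imbalance, as tabulated above. Those figures depend on the assumed SD, deficits and exclusion rates. They show sensitivity and do not predict this trial's bias.

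**What to change.** In both the Patient compliance and the Data analysis sections, delete the statement that low compliers are left out of the final analysis. Replace it with wording such as:

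*The primary (final) analysis is carried out in the FAS, with all randomised women in their allocated arm. An analysis restricted to women with at least 70% compliance is a supportive per-protocol analysis.*

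Then state whether compliance under 70% counts as a serious protocol violation, so that the restricted analysis and the protocol-compliant set are one population. If they are meant to differ, name and define each.

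The change takes a few sentences and no extra data, and should be made before allocation is revealed. Its real cost is the dilution calculated above: power falls just below the stated 90% at about 10% non-compliance and to about 86% at 15%. The team should accept that openly, since the compliers-only analysis avoids it only by giving up the protection of randomisation.
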